### Blinding

#### Participants

All participants will believe that they have been given some form of ‘intervention’ for home use. Irrespective of group allocation, the participants will be given identical packs to take home with them and advised to use them at home. Inside the blank control pack will be the normal patient information leaflet and a colouring book and inside the packs of the other two groups will be the logon information for the online games. The blank control group will be given nothing on the ward on the day of the GA visit and the other two groups will be given a laptop at their bedside with either the hand-washing or GA-coping game. All study patients will have curtains drawn around their beds which is common practice on the busy ward, especially when children are changing clothes. This will avoid contact between participants to avoid contamination and the unblinding of both participants and the blind data collector.

### Blinded observer (RA)

All of the key outcome measures on the day of the GA treatment visit will be collected by a second researcher (RA), blind to the group allocation. These include preoperative anxiety, acceptance of anaesthetic induction, details concerning the operative procedure (such as anaesthetic type), the anaesthetists’ view of patient compliance, service throughput timings, and the family’s satisfaction prior to discharge.

Only the research associate (CH) will be aware of the group allocation. The research associate will carry out the recruitment, consent, and randomization procedures, collect demographic information, and collect baseline measures including psychological wellbeing and dental anxiety (these will only be used to inform equivalence between the groups) at the time of recruitment. They will also deliver the intervention packs and conduct the 48 hour and 1 week follow-up telephone calls.

### DSU staff

The anaesthetist, operating dentist, and the operating theatre and recovery staff will be blinded to the group allocation. It is hoped that they will hardly be able to identify participants from non-participants.

### Statistician

The group allocation will remain concealed until after the statistical analysis has been concluded. The unblinded researcher (CH) will check whether families have used the GA-coping game at home. After this analysis is completed the automated user logs will be further investigated; since the URL logon for each study group family matches their study ID.

### Measures

The primary outcome measures are: (1) child cooperation and distress during the GA dental visit, on the ward before the procedure using the m-YPAS (time 1) (non-blinded researcher/observer reported) and the FIS child-reported to unblinded researcher [18,19]; (2) behaviour at anaesthetic induction by A-VAS score [16] and m-YPAS (time 2), reported by blinded researcher; (3) physical and psychological morbidity postoperatively using the Rutter Scale, Morbidity Checklist, and the Post Hospital Behaviour Questionnaire (unblinded-researcher recorded), parentally reported; (4) parent and child satisfaction using a 10 cm VAS (S-VAS) at the time of discharge from the Day Surgery Unit (parentally reported to the blinded observer) and the Treatment Evaluation Inventory at the 48 hour telephone call (parentally reported to the unblinded researcher); (5) service throughput will be measured using the duration of time in the induction room, duration of time in the recovery room, and duration of time on the ward before discharge (blinded-researcher recorded).

The secondary outcome measures are: the internet package usage by questioning about ease of access, acceptability, satisfaction- by parental reporting to the unblinded researcher at time of delivery of the allocated interventions, on the ward, and automatic recording via the internet.

The measures are detailed further:

At the time of recruitment the Rutter scale will test psychological well-being and status; this is a parental reporting tool but the unblinded researcher will be on hand to assist the parent with the questions if they have difficulty with literacy [23]. The child self-report of dental anxiety using MCDAs [20] supported by the Facial Image Scale (FIS) to aid comprehension [21], will be scored by the child themselves but supported by the unblinded researcher and the parent.

At the time of the GA treatment visit on the DSU ward before being taken into the induction room all child participants will complete the FIS (FIS-ward) to self-report situational anxiety and the Bieri Scale to record pain (toothache) [26] and will be asked about their usage of the intervention. These will be recorded by the unblinded researcher since these families might be using their allocated intervention at this time. The child’s behaviour will be observed by the blinded observer and scored using the modified Yale Preoperative Anxiety Scale (m-YPAS-time 1) approximately 10 minutes before they are due to leave the ward and be taken into the anaesthetic induction room.

The behaviour at anaesthetic induction will be video recorded and the observed behaviour (acceptance of anaesthetic induction via inhalation) scored by the blinded researcher using m-YPAS(-time 2) and a 10 cm Visual Analogue Scale (A-VAS) rounded to the nearest to 0.5; the video recordings will enable future intra-rater reliability and reproducibility testing on the A-VAS [13,17,18].

During the surgical procedure the blinded observer will record the number of teeth extracted, the dose of local anaesthetic administered (routinely given to aid haemostasis), and the dose, preparation and route of analgesics administered (usually paracetamol or NSAIDs rather than opioids).

Service throughput will be reported in respect to the duration of time in the anaesthetic induction room, the duration of time in the recovery room, and the duration of time on the ward prior to discharge. These times are routinely recorded on the computer system at King’s College Hospital by the DSU staff for use in the generation of theatre utilisation data; the data will be recorded and accuracy of the recorded times will be verified by the blinded observer.

In the recovery room, children’s observed behaviour will be scored using a 10 cm Visual Analogue Scale, to differentiate this from the other visual analogue scales used in the study this will be termed R-VAS and will be scored by the blinded researcher.

At the time of discharge, parents will be asked to rate their satisfaction with the preparatory information by the blinded researcher using a series of questions scored using a further 10 cm VAS (S-VAS).

AT 48 hours following the GA, and again one week later, parents will be contacted by the unblinded researcher by telephone in the evening and asked to rate their child’s behaviour and psychological wellbeing using the Rutter Scale [25] and asked to report on morbidity using a Morbidity Checklist (MC) and the Post Hospital Behaviour Questionnaire (PHBQ) [27]. They will also be invited to score their satisfaction with both the preparatory information and the service they received using the Treatment Evaluation Inventory (TEI) [23] and the child will be invited to self-report anxiety using the FIS [21]. Further demographic information will be asked at the one week data capture time point (parent age, highest education qualification, who lives in the house with the child, and whether the parent is a single parent or parents with another person) since it preserves family privacy and is remote from the stressful hospital visits. The family will also be invited to comment in their own words about their satisfaction and express their views on the preparation they received and the service that they experienced. Therefore, the group allocation will be unconcealed to the non-blinded observer.

For the web-based GA-coping game study group, participants’ usage will be captured automatically each time they access the site. Each unique website URL matches the family study ID. These logs will be analysed by one of the grant applicants (PAR) and the grant statistician (ND) after the RCT data has been analysed in full and the code broken.

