**Methods/design:**

The Phase III RCT will use a double-blind three-armed design. The clinical trial will recruit up to 210 children and will compare the web-based game against standard care and another non-medical game. At least 53 patients in each group will be required for 90% statistical power. Distress will be assessed through an evaluation of the child’s behaviour during the visit and later parental reports of physical and psychological morbidity. The satisfaction of parents and children will be measured; the mode of usage of the web-based game will be automatically recorded and the impact on the service (for example, recovery time and throughput) will be reported.

The Phase III study primary outcome will measure: (1) patient experience: acceptance of anaesthetic induction, child cooperation and distress, reduction of peri- and postoperative morbidity, child and family satisfaction, and (2) service improvement: anaesthetic time and improvement in throughput. Measures will be administered at baseline, at the time of the GA treatment visit, and at 48 hours and one week postoperatively.

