### Power calculation

Based on acceptance of anaesthetic induction measured using a 10 cm Visual Analogue Scale (A-VAS), using results from the Phase II study [13] for a statistical power of 90%, and for a difference of 2 cm on the Visual Analogue Scale (SD = 3.1) at the time of anaesthetic induction (an effect size of 0.65), 53 children will be required in each group. We have chosen this measure since it matches the Phase II RCT and has been well used and validated in this setting [15-17].

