### Statistical analysis

Intention-to-treat methodology will be employed. Descriptive statistical summaries for all explanatory variables at baseline will be provided, overall and by study group. Analysis of Variance and Chi-square tests will be used to highlight any significant imbalance between groups. The GA-coping game’s effect on the key primary outcome measures and the 10 cm VAS and the m-YPAS for child behaviour at anaesthetic induction, will be compared with the two controls and will be modelled using linear or ordinal regressions as appropriate. Multivariate models will be fitted so that any confounding effect is assessed and adjusted for if necessary.

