The FIS is well-validated for use, especially in dental settings. It is easy for a child to score this with the support of their parent or carer. It is a sheet of paper with symbols of faces [21]. It is the unblinded researcher who will have to collect this measure from the child on the ward since the child may be using the intervention or discussing it at that time point. Therefore, the researchers are aware that results obtained using this measure must be treated with caution. Indeed, the anxiety, psychological, and demographic data at the time of recruitment, family information such as maternal education and reported toothache on the day of the GA visit, as well as details of the anaesthesia, surgery and recovery, and analgesia will be used to report both equivalence between the groups and explain the patient journey so that the key results can be interpreted in context.

In paediatric dental anxiety studies it has been recommended that multiple measures are used; the researchers have adopted this principal for use in the Phase III RCT [31]. As such, we plan to use child and parent reporting as well as direct observation to record responses to the intervention. There are three key time points: on the ward before the anaesthesia, at the time of the anaesthetic induction, and then later at home. If this was a drug trial it would be easy to keep the data collection on the ward blind throughout, but since this is a computer intervention and the laptop computer will be open on the child’s bed (albeit with the curtains closed), the likelihood of unblinding is high. It is partly for this reason that such a comprehensive pilot study was needed.

Furthermore, ideally, the anaesthetists should be allowed to talk about the intervention with the child at the time of induction as it will help with the patient-doctor communication and engagement. Thus it might help with the anaesthetic induction and give a score in favour of the intervention. However, the researchers believe that blind data collection at this point is vital and so the hospital staff have been asked not to unblind RA.

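### Twelve measures are designated primary and compared with two controls without a decision rule, while the 90% power covers one unadjusted A-VAS contrast

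*Protocol article*

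**What the plan says.** The Measures section begins "The primary outcome measures are: (1) child cooperation and distress during the GA dental visit, on the ward before the procedure using the m-YPAS" and continues through five domains:

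- ward: m-YPAS time 1 and FIS
- induction: A-VAS and m-YPAS time 2
- morbidity: Rutter Scale, Morbidity Checklist and PHBQ
- satisfaction: S-VAS and TEI
- throughput: three durations

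The abstract and the Primary aim describe the primary question in the same multi-domain terms. Only usage, access and acceptability of the internet package are called secondary.

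The Power calculation section is narrower. It is "Based on acceptance of anaesthetic induction measured using a 10 cm Visual Analogue Scale (A-VAS"), "for a statistical power of 90"%, "for a difference of 2 cm on the Visual Analogue Scale (SD = 3.1"), and concludes that "53 children will be required in each group". The Figure 3 legend and the Discussion also tie the sample size to one measure. The abstract gives the figure without an endpoint or a contrast: "At least 53 patients in each group will be required for 90% statistical power".

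The Statistical analysis section says that the effect on the main primary measures, and on the VAS and m-YPAS at induction, "will be compared with the two controls and will be modelled using linear or ordinal regressions as appropriate". It gives no order of testing and does not say how results against the two controls are to be combined. The article states no significance level.

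**The concern.** A primary label decides which result may carry the trial's claim. Here twelve measures hold it equally, and each may be set against two controls. A favourable result on any one of them, against either control, could be reported as a positive primary result without departing from the text. The null hypothesis does not help, because it is one compound statement covering coping, information, morbidity, access and satisfaction.

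The label also puts measures of unequal quality on one footing. On the FIS collected on the ward, the Discussion says that "results obtained using this measure must be treated with caution". It also says that unblinded collection of the TEI must be allowed for in interpretation. Both nonetheless rank level with the A-VAS scored by the blinded observer.

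The missing rule on the two controls affects power as well. The Methods and design section includes the hand-washing game to separate the coping content from distraction by a computer. If the intended claim is that the coping game beats both controls, the power for that claim differs from the power of one pairwise test.

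**Working it through.** **Inputs from the article.** Difference 2 cm, SD 3.1, power 90%, 53 per group (Power calculation). Three arms, target 70 per group (Justification of sample size). 185 recruited (Trial status), and 185/3 is about 61 per group. Primary measures: 2 + 2 + 3 + 2 + 3 = 12 (Measures).

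**Assumptions.** Two-sided 5% per test, equal arms, both controls 2 cm from the study group for the joint power, and a correlation between measures from 0 to 0.9, because the article gives none.

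**Step 1: reproduce the 53.**

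n per group = 2 × (1.960 + 1.282)² × 3.1² / 2² = 2 × 10.51 × 9.61 / 4 = 50.5, so 51. The exact t calculation gives 52.

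Power at 53: 2/3.1 = 0.645; 0.645 × √(53/2) = 3.32; Φ(3.32 − 1.96) = Φ(1.36) = 91.3% (noncentral t: 90.8%).

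The alternatives fit less well. One-sided 5% gives 42, 2.5% per contrast gives 60 (t: 61), and a three-group F test with both controls 2 cm worse gives about 47. The 53 therefore corresponds to one unadjusted two-sided 5% pairwise contrast on A-VAS, and it is sound for that.

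**Step 2: power when there are two controls.** The two contrasts share the study arm, so with equal groups their correlation is 0.5. The power to win both is the joint probability that both statistics exceed the critical value. It was simulated with the variance pooled over three arms.

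| Analysed per group | One contrast | Both controls | At least one |
|---|---|---|---|
| 53 | 91% | 85% | 97% |
| 61 | 94% | 90% | 99% |
| 70 | 97% | 94% | 99% |

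Check at 53: at least one = 2 × 91.0% − 84.8% = 97.2%. A separate bivariate normal calculation gives 61 per group for 90% power against both.

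**Step 3: chance of at least one false positive.** This is 1 − P(every |Z| < 1.96) with no true effect, simulated with the shared study arm.

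| What is tested against both controls | Tests | Correlation 0 | 0.3 | 0.5 | 0.9 |
|---|---|---|---|---|---|
| A-VAS only | 2 | 9% | – | – | – |
| A-VAS and m-YPAS at induction | 4 | 17% | 17% | 16% | 13% |
| All twelve measures | 24 | 68% | 61% | 51% | 23% |

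Check: twelve independent tests against one control give 1 − 0.95¹² = 46.0%, and the simulation gave 46.1%. The Rutter Scale, Morbidity Checklist and PHBQ are each taken at 48 hours and at one week. Counting these separately gives 12 + 3 = 15 outcomes, and the range becomes 25–76%.

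**The case against.** The strongest reply is that significance level, multiplicity method and decision rule are commonly left to the full protocol or analysis plan, neither of which is shown. That stands for the method. It does not stand for the designation: this article itself calls twelve measures primary and powers one.

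Four stronger readings are tempting, and the article does not support them.

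- A reader might infer that the trial's error rate differs from what is stated. No rate is stated, so nothing is contradicted; the rate is undefined.
- A reader might infer that the 90% power is wrong. The Power calculation section ties it to A-VAS with a difference and an SD, and it reproduces. Only the abstract leaves it unqualified.
- A reader might infer that 24 primary tests are planned. The sentence in Statistical analysis is unclear and may limit the modelling to the two induction measures, which is 4 tests.
- A reader might infer that about 60 per group are needed because alpha must be split. That holds only if beating either control suffices. If both must be beaten, or if they are tested in order, no split is needed.

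The practical loss of power may also be small. Trial status reports 185 recruited and less attrition than expected. If about 61 per group were all analysed, power against both controls would be about 90%. The cautions on FIS and TEI are openly disclosed and concern bias rather than multiplicity; they bear here only on whether those measures should be primary. None of this resolves the twelve equal primaries.

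**Conclusion.** The concern holds as a fault in what the article fixes: twelve co-equal primary measures, two controls, no rule, and a sample size built on one contrast. How far the false-positive chance exceeds 5% depends on how the analysis sentence is read and on correlations that the article does not give. It is about 9% at the least, 13–17% on the narrow reading, and 23–68% on the wide one, all at an assumed two-sided 5% per test.

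The sample size itself is not in error. What does not hold is reading the abstract's 90% as power to beat both controls: that is about 85% at 53 per group, assuming the same 2 cm gap to each control. The point should be settled before the allocation code is broken, because afterwards selection among the primaries could not be ruled out.

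**What to change.** Before the allocation code is broken:

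1. Name A-VAS at induction, scored by the blinded observer, as the single primary outcome. The power calculation already implies this.
2. Test it against the two controls in a fixed order stated in advance, each at two-sided 5%, going to the second only if the first is significant. The team should choose and justify the order.
3. Make the other eleven measures secondary, reported with estimates and intervals and without a confirmatory claim.
4. Restate the power as 91% for one pairwise A-VAS comparison and about 85% to beat both controls, at 53 per group, and qualify the abstract's figure in the same way.
5. Report that the change was made after recruitment closed on 4 June 2014.

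The cost is wording only, with no further patients or data. The downsides are that fewer measures can carry a confirmatory claim and that the stated power for beating both controls is slightly lower. Because the reclassification follows data collection, its credibility depends on a dated record that it preceded unblinding.

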### Intra-observer agreement of VAS at induction

Based on a random selection of 36 cases from RCT recruits, the A-VAS measure was rescored by the blinded observer (RA) using direct and video evaluation and confirmed an intra-class correlation coefficient of 87% with a 95% confidence interval of between 79 and 95%. This indicates from very good to excellent intra-observer agreement.

### Power calculation

Based on acceptance of anaesthetic induction measured using a 10 cm Visual Analogue Scale (A-VAS), using results from the Phase II study [13] for a statistical power of 90%, and for a difference of 2 cm on the Visual Analogue Scale (SD = 3.1) at the time of anaesthetic induction (an effect size of 0.65), 53 children will be required in each group. We have chosen this measure since it matches the Phase II RCT and has been well used and validated in this setting [15-17].

### Justification of sample size

We anticipate a dropout rate in the region of 20% and as such, a target group of 70 children for each of the groups is appropriate. Moreover, our previous work has shown that up to 30% of children referred for dental GA might have undergone a GA previously [13,28], and we expect a further 20% will refuse to participate due to concerns about filming, so we anticipate that we may have to approach as many as 300 potential recruits to achieve our target of 210 children.

### Statistical analysis

Intention-to-treat methodology will be employed. Descriptive statistical summaries for all explanatory variables at baseline will be provided, overall and by study group. Analysis of Variance and Chi-square tests will be used to highlight any significant imbalance between groups. The GA-coping game’s effect on the key primary outcome measures and the 10 cm VAS and the m-YPAS for child behaviour at anaesthetic induction, will be compared with the two controls and will be modelled using linear or ordinal regressions as appropriate. Multivariate models will be fitted so that any confounding effect is assessed and adjusted for if necessary.

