### Randomization

Randomization will be by minimisation in terms of year of age at time of recruitment (age groups: 5, 6, or 7) and gender. This will be performed centrally at the Biostatistics and Research Methods Centre of the Dental Institute, King’s College London. This will ensure not only that the proportion of 5, 6, and 7-year-old boys and girls will be balanced each week following each recruitment session, but also that the unblinded researcher cannot bias participant group allocation. The procedure for this has already been detailed in the pilot study.

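### Adjustment is left conditional after baseline significance tests, the minimisation factors are not named in the model, and the limit placed on baseline scores conflicts with it: a cost in precision

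*Protocol article*

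**What the plan says.** Four parts of the protocol article bear on covariate adjustment.

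- **Statistical analysis.** Baseline variables are summarised by group, and "Analysis of Variance and Chi-square tests will be used to highlight any significant imbalance between groups". The effect of the game on the key outcomes "will be compared with the two controls and will be modelled using linear or ordinal regressions as appropriate". Then: "Multivariate models will be fitted so that any confounding effect is assessed and adjusted for if necessary". No covariate is named, and nothing says when adjustment becomes necessary.
- **Randomization.** "Randomization will be by minimisation in terms of year of age at time of recruitment (age groups: 5, 6, or 7) and gender".
- **Blinding, Blinded observer (RA).** Of the psychological wellbeing and dental anxiety scores taken at recruitment: "these will only be used to inform equivalence between the groups".
- **Measures.** "At the time of recruitment the Rutter scale will test psychological well-being and status", and the child reports dental anxiety on the MCDAs at the same visit. The Rutter Scale is also a primary outcome for postoperative morbidity, collected by telephone at 48 hours and one week.

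**The concern.** Under sound random allocation, any baseline difference between arms arises by chance, so a significance test of that difference answers no question the trial needs answered. The choice of covariates should rest on how strongly they predict outcome, and that can be settled in advance. Here adjustment follows an unstated judgement made after the data are seen, next to a set of imbalance tests. Two analysts following the text could fit different models to the same data.

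Minimisation makes the arms similar on age and gender. An unadjusted model does not credit that balance, so its standard error is too large whenever those factors predict outcome. A search for imbalance would rarely pick them up.

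The restriction on the recruitment scores adds a contradiction. If baseline anxiety differed between arms, the Statistical analysis section would invite adjustment and the Blinded observer (RA) section would rule it out. Read literally, the restriction also prevents a primary outcome, the Rutter Scale, from being adjusted for its own baseline value. What is at stake is precision and a reproducible primary model.

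**Working it through.** **Inputs from the documents.** Power calculation section: difference 2 cm on the A-VAS, SD 3.1, power 90%, 53 per group. Alpha and sidedness are not stated there; two-sided 0.05 is assumed.

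**The plan's own figure.** n = 2 × [3.1 × (1.960 + 1.282) / 2]² = 50.5, so 51 per group (52 with the t distribution). This agrees with 53 to within 2. The unadjusted standard error at 53 per group is 3.1 × √(2/53) = 0.602, and power is 91.3% (90.8% with the t distribution). The sample size has no covariate term, so it does not depend on adjustment.

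**Gain from one pre-specified baseline score.** With correlation ρ between score and outcome, the residual SD is 3.1 × √(1 − ρ²). The documents give no ρ, so a range is assumed. Power below uses the normal approximation.

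| ρ (assumed) | Residual SD | Fall in SE | Power at 53 per group |
|---|---|---|---|
| 0.1 | 3.08 | 0.5% | 91.6% |
| 0.3 | 2.96 | 4.6% | 93.6% |
| 0.5 | 2.68 | 13.4% | 97.0% |

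The t-based powers are 93.2% at ρ = 0.3 and 96.7% at ρ = 0.5. For the Rutter outcomes no SD or target difference is given, so only the fall in SE carries over, at whatever ρ applies.

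**Comparison of strategies.** Simulation of three arms with 159 children in all (53 per arm on average), minimisation on age year and gender with an assumed 80% chance of taking the best-balancing arm, and 3,000 runs per scenario. In the test-triggered strategy, the baseline score enters only if a three-group ANOVA gives p < 0.05. The paired figures are assumed correlations with outcome, first for the baseline score and then for the minimisation factors.

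| Strategy | Mean SE, 0.3/0.2 | Type I error | Power | Mean SE, 0.5/0.3 | Type I error | Power |
|---|---|---|---|---|---|---|
| Unadjusted | 0.601 | 0.047 | 91.5% | 0.602 | 0.040 | 91.7% |
| Test-triggered | 0.600 | 0.045 | 91.6% | 0.599 | 0.035 | 92.2% |
| Age and gender | 0.588 | 0.052 | 92.0% | 0.574 | 0.046 | 93.3% |
| Age, gender and baseline score | 0.562 | 0.053 | 93.7% | 0.490 | 0.053 | 98.1% |

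(Mean SE is from the runs with no effect; power is at 2 cm.)

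**Reading the table.** Leaving out age and gender makes the standard error 0.601/0.588 = 1.02 to 0.602/0.574 = 1.05 times what it should be. Test-triggered adjustment recovers almost none of the available precision. Its type I error lies below 5%, so it is somewhat conservative.

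**The case against.** The strongest reply is that the text is milder than it first looks, and much of that reply stands.

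- A reader might infer that p-values decide which covariates enter. No sentence says so. The tests are there to highlight imbalance, and the adjustment sentence comes later, after the outcome models. What can be said is that adjustment is conditional, has no criterion, and so appears data-dependent.
- A reader might infer that age and gender are excluded. They are only unnamed. The article is condensed, and a fuller analysis plan may list them.
- A reader might infer that the recruitment scores are firmly barred from the model. The restriction is a parenthesis in a blinding section, while the Statistical analysis section treats baseline data as explanatory variables. The supportable claim is a conflict between two sections, not a settled exclusion.
- A reader might infer that outcomes will be adjusted for variables measured after allocation, because the Discussion says that "details of the anaesthesia, surgery and recovery, and analgesia will be used to report both equivalence between the groups". That sentence concerns reporting and context; no adjustment for those variables is proposed. Nor need equivalence there mean more than comparability.
- A reader might attach a chance of false alarm to the baseline tests. With independent tests at 5% it is 1 − 0.95^k: 23% for 5 tests and 40% for 10. The number of tests is not in the documents, and nothing makes a significant test the trigger, so the conclusion does not rest on this.

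The harm is also modest: at a correlation of 0.3 or less the baseline score saves under 5% of the standard error, and the unadjusted analysis already exceeds 90% power for the A-VAS. What survives is the testing of baseline imbalance, the open-ended condition on adjustment, and the conflict over the recruitment scores. All three are stated in the article, so a consistent analysis plan would inherit them.

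**Conclusion.** The point holds as one of precision and clarity. Baseline significance tests are planned, adjustment is conditional without a rule, the minimisation factors are not named in the model, and the limit on the recruitment scores contradicts the analysis section and, taken literally, denies the Rutter outcomes their own baseline.

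A stronger reading, that the trial's conclusions or sample size are unsafe, is not supported: type I error is not inflated and the 53 per group is reproduced without any adjustment. The size of the loss rests on correlations that the documents do not give: about 5% of the standard error at an assumed 0.3 and about 13% at 0.5 for a baseline score, plus about 2-5% for age and gender if they correlate 0.2 to 0.3 with outcome. This is a free improvement.

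**What to change.** 1. Drop the ANOVA and chi-square tests of baseline imbalance and present baseline data descriptively by arm.
2. Replace the conditional adjustment sentence with a pre-specified model: arm, age year (5, 6, 7) and gender for all primary outcomes; baseline MCDAs added for the anxiety and induction outcomes (A-VAS, m-YPAS, FIS); baseline Rutter added for the Rutter outcomes. The documents give no basis for adding MCDAs to satisfaction or throughput outcomes.
3. State that only variables measured before allocation may be covariates in the primary models. This is a safeguard, since no such adjustment is proposed at present.
4. Strike the word *only* from the parenthesis in the Blinded observer (RA) section so that it agrees with the Statistical analysis section.

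The cost is wording; every variable is already collected. If a chosen score predicts nothing, the loss is one degree of freedom. Recruitment has closed (Trial status), but the Statistician section keeps allocation concealed until the analysis is finished, so the model can still be fixed if that analysis has not yet been run.
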